## Abstract

**Background:**

Neck pain is a common musculoskeletal complaint and is often associated with shoulder or arm pain. There is a paucity of information on effective treatment for neck and arm pain, such as radiculopathy or cervico-brachial pain. Guidelines recommend neck mobilisation/ manipulation, exercises and advice as the treatment for neck pain, and neck and arm pain. There are a few studies that have used neural mobilisation as the treatment for cervico-brachial pain. Although results seem promising the studies have small sample sizes that make it difficult to draw definite conclusions.

**Methods:**

A randomised controlled trial will be used to establish the effect of neural mobilisation on the pain, function and quality of life of patients with cervico-brachial pain. Patients will be recruited in four physiotherapy private practices and randomly assigned to usual care or usual care plus neural mobilisation.

**Discussion:**

In clinical practice neural mobilisations is commonly used for cervico-brachial pain. Although study outcomes seem promising, most studies have small participant numbers. Targeting the neural structures as part of the management plan for a subgroup of patients with nerve mechano-sensitivity seems feasible. Patients with neuropathic pain and psychosocial risk factors such as catastrophising, respond poorly to treatment. Although a recent study found these patients less likely to respond to neural mobilisation, the current study will be able to assess whether neural mobilisation has any added benefit compared to usual care. The study will contribute to the knowledge base of treatment of patients with cervico-brachial pain. The findings of the study will be published in an appropriate journal.

**Trial registration:**

Trial registration Number: PACTR201303000500157.

**Electronic supplementary material:**

The online version of this article (doi:10.1186/1471-2474-15-419) contains supplementary material, which is available to authorized users.

## Background

Neck pain is one of the most common debilitating musculoskeletal complaints seen in physiotherapy practice [1–3]. In a systematic review on the prevalence of neck pain in the adult population, Fejer et al. found the point prevalence to be 7.6% and the lifetime prevalence to be 48.6% [4]. In the 2010 global burden of disease report neck pain ranked as the fourth highest disease in terms of disability [5].

Neck pain is often associated with headache, upper back and shoulder/arm pain [3, 6]. In a study by Daffner et al. [7] 65.4% of the neck pain population included in their study had arm pain associated with their neck pain. The patients with neck and arm pain were more disabled than patients with only neck pain. Cervico-brachial pain syndrome is an upper quarter pain syndrome in which neural tissue sensitivity to mechanical stimulus is thought to play a role [8, 9]. Different terms are often used to describe patients with upper quadrant pain such as cervico-brachial pain [10], nerve related neck and arm pain [11] and cervical radiculopathy [6, 12]. Diagnosis of cervico-brachial pain is made by a clinical process and there is often no overt neural involvement [8]. Neural involvement can only be assumed if a cluster of clinical findings are present such as an active and passive movement dysfunction, adverse response to neurodynamic testing and evidence of a local cause of neuropathic pain [8, 9].

Neuropathic pain is described as pain initiated or caused by a primary lesion or dysfunction in the nervous system [13]. Neuropathic pain is a problem associated with and prevalent in many musculoskeletal conditions such as low back pain [14], acute or chronic radiculopathy [12] and syndromes such as cervico-brachial pain syndrome [10, 15]. Neuropathic pain is consistently linked to high levels of pain, disability, poor quality of life and poor response to treatment [14, 16, 17] and is therefore a difficult condition to treat successfully [14, 16].

Psychosocial factors have also been shown to play an important role in treatment outcomes [18–21]. Pool et al. [19] examined the influence of different psychosocial factors on treatment outcome and found fear of movement to be significantly correlated with poor outcomes in the short and long term. In a study by Karels et al. catastrophising was significantly linked to persistent symptoms of neck pain over a six-month period [22]. Catastrophising is a cognitive process that includes elements of magnification, helplessness, pessimism and is a consistently important predictor of poor pain-related outcomes [23]. Verhagen et al. [20] explored the influence of various factors on treatment outcome in neck pain and found pain severity and catastrophising to be the most important determinants for poor recovery. In a study to examine factors influencing return to work in patients with neck/arm/shoulder pain, the authors also concluded that psychosocial factors should be taken into account when interventions are planned [18]. Similar to these findings Thompson et al. [24] found catastrophising and poor self-efficacy to be associated with higher pain and disability. Other factors that have been shown to influence treatment outcomes are pain intensity at baseline, increased age and the presence of low back pain [25, 26].

Most clinical guidelines do not differentiate between treatment for neck pain and neck and arm pain such as cervico-brachial pain [27]. The American Physical Therapy Association recommends mobilisation/ manipulation of the neck and thoracic spine, exercises and education in the management of neck pain [27]. The findings of a recent Cochrane review confirm the above recommendations [28]. The American guidelines [27] also recommend that neural mobilisation should be considered for patients with neck and arm pain (level B evidence).

Neural mobilisations (NM) are often used to affect the neural structures in conditions with signs of neural involvement or neural mechano-sensitivity [10, 11]. NM is said to affect the axoplasmic flow [29], movement of the nerve and its connective tissue [30], and the circulation of the nerve by alteration of the pressure in the nervous system and dispersion of intraneural oedema [31]. NM can also decrease the excitability of dorsal horn cells [32]. NM is defined as interventions aimed at affecting the neural structures or surrounding tissue (interface) directly or indirectly through manual techniques or exercises. The interface can be mobilised by mobilising the tissue surrounding the nerve, along the course of the nerve [33]. Although it is a technique used in clinical practice the use thereof in the literature could only be identified in a case report of a patient with cervical radiculopathy [34]. The treatment was combined with manual therapy and exercises, both treatments which have been shown to be effective for cervical radiculopathy [28]. It is therefore difficult to know whether the NM contributed to the treatment effect. The effectiveness of this form of NM has therefore yet to be established. In cervico-brachial pain, neural tissue sensitivity to mechanical stimulus is thought to play a role [8], it can therefore be reasoned that targeting the neural structures specifically should be an important aim of treatment in patients with cervico-brachial pain.

The efficacy of NM has been studied in various populations such as low back pain [35], carpal tunnel syndrome [36], lateral epicondalalgia [37] and cervico-brachial pain [10, 11, 15]. The NM techniques used for cervico-brachial pain consisted of cervical lateral glides and neural gliding exercises [10, 15, 38]. According to a systematic review of NM, the evidence for the efficacy of NM is limited [39].

### Aims of study

The aims of the study are firstly to establish the effect of NM on the pain, function and quality of life of patients with acute and sub-acute cervico-brachial pain. Secondly it aims to establish if high catastrophising scores and neuropathic pain have an influence on treatment outcomes.

### Study design

A randomised controlled trial will be used to answer the research questions. The study will comprise of two groups, a control group and an experimental group. The control group will receive “usual care” (UC) [40] as identified by a review of the literature. The intervention group will receive neural mobilisation in addition to the usual care.

### Subjects

#### Selection procedure

Patients will be recruited from private physiotherapy practices, which have agreed to take part in the study. These practices will be situated in the Pretoria region, Gauteng, South Africa. Patients are referred to private practices by general practitioners or may be self-referred. Patients presenting with cervico-brachial pain will be screened for eligibility and if eligible will be invited to take part in the study (Figure 1).

**Figure 1 Fig1:**
[figure not shown]
**Screening and allocation of patients.**

To be included in the study patients must be over the age of 18, with cervico-brachial pain as defined by Hall and Elvey [8]. This includes at least five of the following characteristics; antalgic posture, active movement dysfunction, passive movement dysfunction which correlate with the active movement dysfunction, adverse responses to neurodynamic tests which must relate specifically and anatomically to the active and passive movement dysfunction, and mechanical allodynia in response to palpation of specific nerve trunks. Lastly evidence from the physical examination of a local cause of the neurogenic pain must be present [8]. The upper limb neurodynamic test 1 (ULNDT1) will be considered positive if the patient’s pain is reproduced or partially reproduced by the test and changed by structural differentiation [41]. Patients with pain from recent onset (one day) up to 12 weeks, recurrent or first incident will be considered for inclusion. Patients with bilateral arm pain will also be considered for inclusion if they comply with the other inclusion criteria. Pain due to injury and the duration of pain will be recorded in the demographics questionnaire that patients will complete.

Patients who do not have a positive neurodynamic test will not be included in the study. Patients will be excluded from the study if they have had previous surgery or recent fractures of the cervical spine, serious neurological signs such as signs of spinal cord pressure or involvement of more than two nerve roots, conditions with long tract signs and those caused by other pathological diseases such as rheumatoid arthritis, neurological diseases, stroke, cerebral palsy, carcinoma or other red flags.

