### Sample size

Primarily this study sets out to assess whether, 6 weeks after onset of treatment the Numerical Pain Rating Scale NPRS score in the intervention group is reduced compared to the UC group. A blocked 2:1 ratio randomisation for intervention to usual care will be done using a computer generated random number list. A sample size of 68:34 i.e. a total sample of 102 patients will have 90% power to detect a clinically relevant increase of 2 for the change from baseline at six weeks in the NPRS score. A standard deviation of 2.05 was assumed as derived from the effect size reported by Bolton and Wilkinson [42]. The standard deviation was furthermore inflated by √2 since change from baseline is of interest. A dropout rate of 15 – 20% was assumed. One-sided testing will be done at the 0.05 level of significance. (nQuery advisor 7).

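### Pain duration at entry ranges from one day to 12 weeks and is recorded, but the six-week ANCOVA does not adjust for it; the NPRS floor also needs acknowledging

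*Protocol article*

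**What the plan says.** Under Screening and allocation of patients, entry rests on age, at least five clinical characteristics, a positive neurodynamic test and symptom duration: "Patients with pain from recent onset (one day) up to 12 weeks, recurrent or first incident will be considered for inclusion". The text shown sets no minimum NPRS (Figure 1 is not shown). The same section adds: "Pain due to injury and the duration of pain will be recorded in the demographics questionnaire". Initial assessment again lists duration of symptoms among the items of the demographic questionnaire.

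The Data analysis section compares the groups on change from baseline at six weeks in NPRS, PSFS and EQ-5D by ANCOVA. It names three kinds of covariate: the baseline score, catastrophising (yes or no) and neuropathic pain (yes or no). Duration is not among them. The Randomisation section describes blocks of 6 at 2:1 and names no stratification by duration.

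The Sample size section states that 102 patients (68:34) "will have 90% power to detect a clinically relevant increase of 2 for the change from baseline at six weeks in the NPRS score". Outcome measures gives the NPRS as a scale from 0 to 10.

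**The concern.** A patient whose pain began yesterday and one whose pain has lasted almost 12 weeks may have quite different expected scores six weeks later, whatever the allocation. If so, leaving duration out of the model puts that spread into the residual variance, and a chance imbalance in duration between arms of about 54 and 27 completers goes uncorrected. The information is already collected before randomisation.

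A related point concerns reading the result. The scale stops at 0 and both arms receive active care. Patients who enter with low scores have little room to show a further benefit, so the mean difference observed on the NPRS can be smaller than the underlying effect. A result of, say, 1.4 points could then be judged not clinically relevant against the 2-point benchmark, although part of the shortfall comes from the scale.

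**Working it through.** **1. The plan's own sample size.** Inputs from the Sample size section: difference 2, SD 2.05 × √2 = 2.899, one-sided 0.05, power 90%, allocation 2:1, dropout 15 to 20%.

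Control n = (1 + 1/2) × SD² × (1.645 + 1.282)² / 2² = 1.5 × 8.405 × 8.565 / 4 = 26.99, so 27. Intervention 54, total 81 evaluable. With 20% dropout, 81 / 0.80 = 101.25, so 102. The stated figure is reproduced.

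**2. What a duration covariate could gain.** If duration explains a share R² of the variance left after the planned covariates, the variance of the treatment estimate is multiplied by (1 − R²) and the effective sample size by 1 / (1 − R²). The documents give no R², so a range is assumed.

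| Assumed partial R² | Effective sample size | Equivalent of 81 completers |
|---|---|---|
| 0% | 1.00 | 81 |
| 5% | 1 / 0.95 = 1.05 | 85 |
| 10% | 1 / 0.90 = 1.11 | 90 |

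The cost is one degree of freedom. With intercept, treatment and three covariates, 81 completers leave 81 − 5 = 76 residual degrees of freedom; with duration, 75. If duration predicts nothing, the loss of information is of the order of 1/75, about 1%.

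**3. Chance imbalance.** The standard error of the between-arm difference in a covariate, in SD units, is √(1/27 + 1/54) = 0.24. Assume a baseline to six-week correlation of 0.5, so that the residual SD is 2.05 × √0.75 = 1.78. At a partial R² of 10%, a typical imbalance moves the NPRS estimate by √0.10 × 1.78 × 0.24 = 0.13 points in either direction. This is the same gain as in step 2 seen within a single trial. It is not a bias over repeated randomisations.

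**4. The floor.** Simulation: latent baseline normal with mean m and SD 2.05; latent six-week mean m minus the usual-care fall, and a further 2 points lower with neural mobilisation; SD 2.05; correlation 0.5; scores rounded and clipped to 0 to 10. The values of m, the fall and the correlation are assumptions.

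| Baseline mean | Usual-care fall | Share at NPRS 2 or less | Observed difference, all | Observed difference, NPRS 3 or more |
|---|---|---|---|---|
| 4 | 1 | 23% | 1.66 | 1.77 |
| 4 | 2 | 23% | 1.36 | 1.52 |
| 4 | 3 | 23% | 1.00 | 1.16 |
| 5 | 1 | 11% | 1.84 | 1.89 |
| 5 | 2 | 11% | 1.66 | 1.73 |
| 5 | 3 | 11% | 1.36 | 1.45 |
| 6 | 1 | 4% | 1.94 | 1.95 |
| 6 | 2 | 4% | 1.84 | 1.87 |
| 6 | 3 | 4% | 1.66 | 1.69 |

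A latent 2 points is observed as about 1.0 to 1.9. Restricting to NPRS 3 or more recovers about 0.01 to 0.16 points.

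**5. Power under the same model.** With ANCOVA on baseline, 54:27 completers, one-sided 0.05 and no entry threshold, simulated power is about 98% in the worst row (mean 4, fall 3) and above 99% in the others. The floor shrinks the residual SD along with the difference, and the plan was sized on the larger SD of 2.90. If a threshold of 3 simply removes patients from a fixed screened pool, power in the worst row falls from about 98% to about 96%; elsewhere it is slightly lower or essentially unchanged.

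**The case against.** On the covariate, the other side is that nothing here is an error. Randomisation balances duration in expectation, the ANCOVA already adjusts for baseline pain, and no figure shows that duration is prognostic. Where the Background lists other influences on outcome, it names baseline pain intensity, age and low back pain, not duration. All of this stands, and it is why the gain is given as a range that starts at zero. What remains is that the variable is already collected, spans a wide range by design and costs almost nothing to include.

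On the floor, a reader might infer more than the documents support:

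- That mild cases cannot show the targeted gain. This is strictly true only for a baseline of 0 or 1. Above that, it depends on the usual-care fall, which is not given. The 2 points are also a difference between group means, not a gain that each patient must make.
- That early pain here mostly resolves by itself. The documents do not say so; the Background links neuropathic pain to high pain levels and poor response to treatment.
- That the trial loses its 90% power. Power falls below 90% throughout if the diluted difference is combined with the planning SD of 2.90 (about 43% at a difference of 1.0), but a model with a floor does not keep that SD. Unadjusted change scores fall below 90% only in the worst scenario (about 72% at mean 4, fall 3), and that is not the planned analysis.
- That a minimum NPRS is needed at entry. It recovers little, would exclude about 4 to 23% of eligible patients under the assumed baselines, and narrows the acute and sub-acute population named in the aims. The required signs and positive neurodynamic test already limit very mild cases to some degree, though they set no score.

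**Conclusion.** The point holds as a low-cost improvement to the analysis with a note on interpretation. Duration runs from one day to 12 weeks, is recorded before allocation, and is absent from the covariates named for the six-week ANCOVA. Including it is worth 0 to 11% in effective sample size if its partial R-squared is 0 to 10%. That range is an assumption.

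The secondary remark also holds. With no minimum NPRS, a latent 2-point effect would be observed as about 1.0 to 1.9 points, given assumed baseline means of 4 to 6, usual-care falls of 1 to 3 and a correlation of 0.5. This affects how the estimate is read against the 2-point benchmark. It does not show that the stated power is lost or that the sample size is wrong: 102 is reproduced, and simulated ANCOVA power stays at about 98% or more.

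**What to change.** In the Data analysis section, add duration of pain at baseline, for example as log days, to the prespecified covariates of the six-week ANCOVA, and do so before outcome data are examined by group. The log is defined throughout, since the shortest eligible duration is one day. The cost is one degree of freedom and no new data collection, provided the questionnaire records duration in days or weeks; broad categories would use one or two more degrees of freedom.

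Add a sentence that the NPRS floor may make the observed difference smaller than the underlying effect, and that this will be considered when the result is compared with 2 points. Optionally, prespecify a supplementary comparison in patients with baseline NPRS of at least 3. It needs no extra data but has fewer patients, so it should not replace the main analysis. No change to the entry criteria or to the sample size is required on this ground.

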### Sample size

Primarily this study sets out to assess whether, 6 weeks after onset of treatment the Numerical Pain Rating Scale NPRS score in the intervention group is reduced compared to the UC group. A blocked 2:1 ratio randomisation for intervention to usual care will be done using a computer generated random number list. A sample size of 68:34 i.e. a total sample of 102 patients will have 90% power to detect a clinically relevant increase of 2 for the change from baseline at six weeks in the NPRS score. A standard deviation of 2.05 was assumed as derived from the effect size reported by Bolton and Wilkinson [42]. The standard deviation was furthermore inflated by √2 since change from baseline is of interest. A dropout rate of 15 – 20% was assumed. One-sided testing will be done at the 0.05 level of significance. (nQuery advisor 7).

### Ethical considerations

Written consent to take part in the study will be obtained from all study participants and they will receive an information sheet explaining the study. Written consent will be obtained from treating physiotherapists. Ethical approval for the study was obtained from the Human Research Ethics Committee of the University of the Witwatersrand, Johannesburg, South Africa.

### Outcome measures

The treating physiotherapist will administer the first set of questionnaires. Treatment randomisation will only be done as described above, after initial measures have been taken. All subsequent follow up questionnaires will be administered by a research assistant who will be blinded to group allocation as the follow up questionnaires at three weeks and six weeks will be done telephonically. The primary outcomes are pain (Numeric Pain Rating Scale), function (Patient Specific Functional Scale) and quality of life (EuroQual Instrument). These self-report outcomes will be followed up at three weeks, six weeks, six months and 12 months.

The NPRS will be used to measure the patient’s pain. The NPRS is an 11-point scale where patients are asked to rate their pain as 0 representing “no pain” and 10 “worst pain possible”. In a study comparing three pain measures [42]. Bolton and Wilkinson [42] found the NPRS to be the most responsive pain measure with an effect size of 0.86 [42]. The validity of the NPRS in an acute setting was established by Bijur et al. [43] and is strongly correlated with the visual analogue scale (r = 0.94, 95% Confidence Interval 0.93 – 0.95) [43]. The NPRS is as sensitive to change as the visual analogue scale which is currently considered the “gold standard” [44].

The Patient Specific Functional Scale (PSFS) will be used to measure disability. The PSFS is a self-report measure to rate activity limitation and function. Patients are asked to nominate three to five activities that are difficult to perform and rate them on an 11 point scale where 0 equals “unable to perform activity” and 10 represents “able to perform activity as before”. The scale was initially developed for patients with back pain and validated for patients with neck pain by Westaway et al. [45]. The scale has excellent validity (r = 0.73 - 0.83) when compared to the Neck Disability Index [45]. The test retest reliability coefficient is excellent (ICC = 0.97) [46]. Cleland et al. [47] compared the Neck Disability Index (NDI) and the PSFS in patients with cervical radiculopathy and found that the PSFS was more responsive than the NDI in this population [47]. In their study the test-retest reliability coefficient was good (ICC 0.82). The scale is commonly used in physiotherapy practice [48].

EuroQuol Instrument (EQ-5D) is a quality of life measurement and will be used to rate the quality of life of study participants. It has two sections: the first part consists of five sections namely mobility, self-care, usual activities, pain/discomfort and anxiety/depression. Each section is rated by three descriptions from “I have no problem” to “I am unable”. The second section of the questionnaire has a 20 cm Visual Analogue Scale with “best imaginable health state” at the one end and “worst imaginable health state” at the other end. The validity was established by measuring it against the SF-12 and positive correlations were found (r = 0.41). It has excellent reliability (ICC 0.82) [49]. Peolsson et al. [50] measured quality of life using the EQ5D in patients with cervical radiculopathy and whiplash associated disorder and found health related quality of life worse in these populations compared to a healthy group.

Patients will be asked to complete the Global Rating of Change Scale (GROC) six weeks after treatment has commenced. This scale measures the patient’s impression of improvement after an intervention. According to a review there are eight different scales [51]. In this study an 11 point Likert scale will be used with −5 representing very much worse, 0 is unchanged and +5 is fully recovered [51]. The test-retest reliability coefficient is good (ICC of 0.9). The scale correlates significantly with changes on the Roland Morris, Oswestry, Pain Rating Scale and the EQ-5D. According to Kamper et al. the Minimal Clinically Important Change of the GROC is two points on an 11 point scale [51]. Patients with a score of +3 or more will be considered “responders” and those with a lower score as “non-responders”.

Two questionnaires will be used to establish which patients have neuropathic pain and which patients are catastrophisers. These questionnaires will be repeated at six months and 12 months to measure if any change has taken place from initial assessment to one year follow up.

The Neuropathic Pain Diagnostic questionnaire (DN4) consists of two sections namely an interview and examination. The interview has two questions, the first about the characteristics of the pain (e.g. burning) and the second about associated symptoms (such as pins and needles) to which the answer is either yes or no. In the examination, tests for hypoesthesia to touch and prick in the painful area as well as whether or not brushing aggravates the pain, are done. Each positive scores a point with a total score of 10. A patient with a score of 4/10 or more can be diagnosed with neuropathic pain [40]. The sensitivity of the test at the cutoff of four is 82.9 and the specificity is 89.9. The inter-rater reliability has Kappa values of between 0.70 and 0.96 [40]. This test have been used successfully in a South African population that are not all English first language speakers [52]. The questionnaire is recommended for use in the South African Guidelines for management of neuropathic pain [53].

The Pain Catastrophising Scale (PCS) is a questionnaire that establishes the levels of catastrophising present in patients. The questionnaire has three components: magnification, rumination and helplessness. Participants are asked to reflect on past painful experiences and to indicate the degree to which they experienced each of 13 thoughts or feelings when experiencing pain. It is scored on a 5-point scale from 0 “not at all” to 4 “all the time” with a maximum score of 52. A score above 24 classifies the patient as a catastrophiser [23]. The internal consistency of the three subscales are Crohnbach’s α of Rumination α = 0.85, Magnification α = 0.75 and Helplessness α = 0.85 [54]. The reliability as tested by Osman et al. [54] could correctly identify 77.1% of the cases. Osman et al. [54] also confirm the findings of Sullivan et al. [23] that the three dimensions represent a single construct.

The Upper Limb Neurodynamic Test 1 (ULNDT1) is described as the straight leg raise test of the arm [33]. The upper limb nerves are elongated and moved in their nerve bed [55] as was verified in an in vivo study. The test consist of different components of movement: patient supine, neck in neutral, shoulder abduction to +/− 110°, extended wrist and fingers, forearm supination, shoulder lateral rotation and the amount of elbow extension is then measured [33]. The reliability of measuring onset of pain and sub-maximal pain in a clinical setting in patients with cervico-brachial pain was established as excellent by Coppieters et al. (ICC ≥ 0.98; SEM ≤ 3.4°) [56]. It is a valid way of identifying patients with a peripheral neuropathic pain component [41]. The ULNDT1 will be assessed again at six months and 12 months.

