### Statistical considerations

Primarily this study sets out to assess whether, six weeks after onset of treatment the NPRS score in the intervention group is reduced compared to the UC group. The sample size calculation is reported for the NPRS, which require the largest sample size.

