### Data analysis

The data summary will employ descriptive statistics, means, standard deviations and 95% confidence intervals and will be reported by study group (intervention & standard care) for the NPRS, PSFS and EQ-5D. Catastrophising (yes & no) and neuropathic pain (yes & no) will be summarised using frequencies, percentages, cross tables and 95% confidence intervals.

Two treatment groups will be compared with respect to the change from baseline at six weeks in the NPRS, PSFS and EQ-5D scores using an analysis of covariance (ANCOVA) with baseline scores, catastrophising (yes & no) and neuropathic pain (yes & no) as covariates. For the total assessment period of 12 months the interaction between visits and treatment will be assessed with respect to NPRS, PSFS and EQ-5D scores in a linear mixed model analysis. Testing will be done at the 0.05 level of significance. For all data description and analyses an intention-to-treat analysis will be performed.

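### The protocol contradicts itself on its primary outcome: one question (NPRS at six weeks) in two sections, three primary outcomes in another, and no rule for what counts as success.

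*Protocol article*

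**What the plan says.** Three parts of the protocol article bear on what is primary.

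- **One primary question.** The Sample size section begins "Primarily this study sets out to assess whether, 6 weeks after onset of treatment the Numerical Pain Rating Scale NPRS score in the intervention group" and goes on to a comparison with usual care. Statistical considerations repeats it: "Primarily this study sets out to assess whether, six weeks after onset of treatment the NPRS score in the intervention group is reduced". The total of 102 (68:34) is calculated for this comparison. The reason given for using this scale is: "The sample size calculation is reported for the NPRS, which require the largest sample size".
- **Three primary outcomes.** Outcome measures states: "The primary outcomes are pain (Numeric Pain Rating Scale), function (Patient Specific Functional Scale) and quality of life (EuroQual Instrument". It then lists follow-up at three weeks, six weeks, six months and 12 months without marking one of these times as primary.
- **One analysis for all three.** Data analysis says: "Two treatment groups will be compared with respect to the change from baseline at six weeks in the NPRS, PSFS and EQ-5D scores using an" ANCOVA. It adds: "Testing will be done at the 0.05 level of significance". That section does not give the sidedness. The Sample size section does: "One-sided testing will be done at the 0.05 level of significance".

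**The concern.** The primary outcome decides whether the trial is called positive, so it has to be settled before any data are seen. Here two incompatible statements stand side by side.

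Suppose NPRS misses 0.05 at six weeks and PSFS reaches it. Under Sample size and Statistical considerations the trial has failed on its primary question. Under Outcome measures it has a significant primary outcome. Two careful readers could report opposite conclusions, each citing the protocol. The choice could then be made after the results are known, and in that case the stated 0.05 would no longer describe the error rate of the primary claim.

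**Working it through.** **1. Reproduce the sample size, to see which reading it supports.**

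Inputs from the Sample size section: difference 2; SD 2.05 × √2 = 2.90 (variance 2 × 2.05² = 8.405); one-sided 0.05; 90% power; 2:1 allocation; dropout 15–20%.

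Normal approximation, usual-care arm:

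n = (1 + 1/2) × (1.645 + 1.282)² × 8.405 / 2² ≈ 27.0, so 27 usual care + 54 intervention = 81.

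With 20% dropout: 81 / 0.80 = 101.25, rounded up to 102 (34:68). The stated figure is reproduced for one comparison, NPRS, at the full 0.05. (Two-sided 0.05 without dropout inflation also gives 34 + 68 = 102. That too is a single comparison at full alpha.)

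**2. Error rate under each possible success rule.**

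The documents give no correlations between the three outcomes, so these are assumed, equal for each pair and not negative, with each scale signed so that positive means benefit. There is no true effect on any scale.

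- *NPRS alone:* 5%.
- *All three required:* at most 5%, because the joint event cannot be more likely than any one of its parts. At correlation 0.5, one-sided, it is 0.5%.
- *Any one of three, independent, one-sided 0.05:* 1 − 0.95³ = 0.143.
- *Any one of three, independent, two-sided 0.05, counting only false claims of benefit:* 1 − 0.975³ = 0.073. The comparable figure for NPRS alone is 0.05 / 2 = 0.025.
- *Any one of three, correlated:* 1 − Φ₃(c, c, c; ρ), where Φ₃ is the trivariate normal distribution function and c = 1.645 (one-sided 0.05) or 1.960 (benefit side of two-sided 0.05).

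| Assumed correlation | Any one of three, one-sided 0.05 | Any one of three, false benefit under two-sided 0.05 |
|---|---|---|
| 0 | 14.3% | 7.3% |
| 0.3 | 13.0% | 6.8% |
| 0.5 | 11.8% | 6.3% |
| 0.7 | 10.3% | 5.5% |
| 0.8 | 9.3% | 4.9% |
| 0.9 | 8.0% | 4.2% |

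**3. What keeping three primary outcomes would cost.**

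Take an equal split, 0.05/3 per outcome, one-sided. With 34:68 the standardised NPRS difference is 2 / (2.90 × √(1/34 + 1/68)) ≈ 3.28 and the critical value is 2.13. NPRS power is Φ(3.28 − 2.13) ≈ 87.6% with all 102 patients. It is 82% after 15% dropout and 79% after 20%, and 90% would need 111 completers. The planned size therefore gives its stated power only when NPRS is tested at the full 0.05.

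**The case against.** The strongest reply has four parts.

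*No any-one rule is written.* A reader might infer that the trial's false-positive rate simply is 10–14%. The documents do not support that. Outcome measures lists outcomes and visit times and states no success rule. On the single question in the other two sections the rate is 5%. Even under an any-one rule, the range needs one-sided tests and correlations no higher than about 0.7. EQ-5D contains a pain/discomfort item and a usual-activities item, so its overlap with NPRS and PSFS could be substantial. This objection stands, and the error rate can be given only conditionally.

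*Sidedness.* Data analysis does not say one-sided. If it means two-sided, counting every rejection would include results favouring usual care, which are not false claims of benefit. This also stands, and the 7.3% ceiling reflects it.

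*A multiplicity rule may sit in an analysis plan that is not shown.* That is fair, and its absence from a condensed article is not the complaint. The article itself says both that there is one primary question and that there are three primary outcomes, and an unseen document does not remove that conflict.

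*Two sections point to NPRS, so the list of three is loose wording.* This is possible, but the text gives the other reading real support. The first aim puts pain, function and quality of life on equal footing. Sizing on the scale said to need the most patients is also how one sizes a trial with several primary outcomes.

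**Conclusion.** The contradiction is real and needs correcting: the number of primary outcomes, and with it the criterion for success, is not settled. Its size depends on the missing rule. The error rate is 5% if NPRS alone is primary and no more than 5% if all three are required. If any one suffices with one-sided tests, it is 14.3% under independence, falling to 8.0% at correlation 0.9. If the tests are two-sided, a false claim of benefit on any of the three has probability 7.3% or less.

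These figures rest on assumed, equal, non-negative correlations and no effect on any scale. They bound what the ambiguity permits and do not measure the trial's actual error rate. The conflict itself rests on the wording alone and needs no assumption.

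**What to change.** In Outcome measures, name the change from baseline in NPRS at six weeks as the single primary outcome, tested at the full 0.05. List PSFS and EQ-5D, and all three scales at three weeks, six months and 12 months, as secondary. Mark the same distinction in Data analysis.

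If PSFS and EQ-5D at six weeks are meant to support confirmatory claims, test them only once NPRS is significant, either in a fixed order or by Holm between those two alone. Holm across all three would not be free: NPRS could then have to pass at 0.05/3, with the loss of power shown above.

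The change is one of wording. The sample size of 102 and its stated power are kept. The one thing given up is that a result on PSFS or EQ-5D alone can no longer be reported as a primary success.
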